#### Primary endpoints

The primary endpoints of the NINCFB are quality of life (St George’s Respiratory Questionnaire, SGRQ scores) and the number of exacerbations during the follow-up period. The SGRQ, a comprehensive questionnaire to estimate pulmonary symptoms and living conditions, is commonly used to assess a patient’s quality of life [22, 23] and has good psychometric properties for the NCFB [24]. Exacerbation of NCFB is defined by the British Thoracic Society as acute deterioration (usually over several days) with worsening local symptoms (cough, increased sputum volume or change in viscosity, increased sputum purulence with or without increasing wheezing, breathlessness, or haemoptysis) and/or systemic upset [25]. This study has two variables designed to determine whether the long-term effectiveness of NAC achieves the treatment goal of NCFB (Table 2).

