### Statistical analysis

The resulting data will then be analysed with SPSS V.26 by statistical experts. Primary outcomes of each group will be compared by Student’s t test (t test) or the Wilcoxon rank-sum test after calculating its normal distribution and will be expressed in terms of the mean, standard deviation (SD) or median to indicate the long-term efficacy of NAC for NCFB. The comparison between the NAC group and the control group in terms of 16S rRNA and the levels of inflammatory factors and oxidative stressors will be of vital importance. In addition, NINCFB will also use the t-test, chi-square test and Wilcoxon rank-sum test to evaluate baseline discrepancy and other variables. Regression analysis and the correlation coefficient may confirm the predictors of disease progression and indicators of NAC efficacy.

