### Sample size

We calculate the sample size required for the evaluation of primary outcome-1 (SGRQ scores) and primary outcome-2 (number of exacerbations) respectively. As NAC is effective in reducing sputum of patients with NCFB in clinical practice, we design a ratio of 2:1 for the sample size of intervention group to control group in this study so that two-thirds of enrolled patients could receive effective treatments. For the SGRQ score, we regard mean difference (MD) of 6 points of SGRQ score as the smallest clinically important difference between two group with a standard deviation (SD) of 8.5 used in the calculation, according to the previous report of NAC on patients with COPD [35–37]. Based on 90% power with a two-sided significance level of 5%, a sample size of 64 for intervention group and 32 for control group is needed as calculated by the software PASS 15. In addition, assuming 20% of patients in each group may drop out or lose data integrity, we need to recruit 79 in the intervention group and 40 in the control group. For the number of exacerbation, we regard MD of 0.7 times of exacerbation per year as the smallest clinically important difference between two group with a SD of 1 used in calculation, according to the published study of NAC on patients with postinfection or idiopathic bronchiectasis [21]. Considering 20% dropout, we also need to recruit 79 patients in NAC group and 40 patients in placebo group (α = 0.05, 1 - β = 0.9). Taken together, this study eventually aims to enroll 119 participants, of them, 79 in the NAC group and 40 in the placebo group.

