### Randomisation and double-blind

Allocation will follow a computer-generated block randomisation list compiled by a biostatistician. The randomisation drug numbers will be sealed in opaque envelopes. All envelopes will be filed with the corresponding CRFs after use. Researchers and patients will not be informed about the specific randomisation. To ensure concealment of allocation, a study designer who is not involved in the trial implementation and data analysis is responsible for the randomisation list. Unblinding and data analysis will be started after all the participants finish the follow-up.

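### A normality check on the outcome data picks the primary test and leaves the summary open, so the exacerbation result may not be readable against the 0.7 mean difference used for sizing

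*Protocol article*

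**What the plan says.** The Primary endpoints section names "quality of life (St George’s Respiratory Questionnaire, SGRQ scores) and the number of exacerbations during the follow-up period". The Statistical analysis section gives one rule for both: a Student t test "or the Wilcoxon rank-sum test after calculating its normal distribution". Results "will be expressed in terms of the mean, standard deviation (SD) or median". No normality test or threshold is named, and nothing says which summary goes with which test.

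The Sample size section plans both endpoints on means. For SGRQ, "we regard mean difference (MD) of 6 points of SGRQ score as the smallest clinically important difference", "with a standard deviation (SD) of 8.5 used in the calculation". For exacerbations, "we regard MD of 0.7 times of exacerbation per year as the smallest clinically important difference", "with a SD of 1 used in calculation". Both use 5% significance and 90% power with 2:1 allocation. The evaluable numbers, stated for SGRQ, are 64 and 32.

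The section on randomisation and blinding adds: "Unblinding and data analysis will be started after all the participants finish the follow-up". As written, nothing places the normality check before treatment codes are known.

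**The concern.** The trial was planned to detect a difference in means, but the stated rule lets the observed distribution decide whether a comparison of means is made. The number of exacerbations in a year is a small whole number, so a formal normality test will almost certainly reject it and the rule then leads to the rank-sum test. That test asks whether values in one arm tend to be higher than in the other. A reader could not tell from its result whether the benefit reached the 0.7 per year that the plan calls the smallest important difference. A median may not help, because medians of small counts move in whole or half steps and can be identical while the mean rates differ.

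What is at stake is mainly a primary result that can be interpreted against its own planning value, and secondarily some power on that endpoint.

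**Working it through.** **1. The planned size is a comparison of two means.** With 2:1 allocation the control-arm number is n = (1 + 1/2) × (1.960 + 1.282)² × (SD/difference)².
- SGRQ: 1.5 × 10.51 × (8.5/6)² = 31.6, so 32 and 64, as stated. Power at 32:64 is 0.903 (0.897 with the t distribution).
- Exacerbations: 1.5 × 10.51 × (1/0.7)² = 32.2, so 33 and 66 when rounded up. At 32:64 the power is 0.899 (0.893 with the t distribution).
- Dropout: 64/0.8 = 80 and 32/0.8 = 40, against the stated 79 and 40.

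The plan's figures are therefore reproduced, and they are powers for a test on means.

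**2. What the rule does to counts.** The protocol gives no arm means or dispersion, so these are assumed, always with a true mean difference of 0.7. Each row is 3,000 simulated trials with 32 control and 64 NAC patients. Shapiro-Wilk was applied in each arm at 5%, and rejection in either arm sends the comparison to the rank-sum test. For the negative binomial (NB), variance = mean + a × mean².

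| Assumed counts, control v NAC | SD, control/NAC | Student t | Welch t | Rank-sum | Equal medians |
|---|---|---|---|---|---|
| Rounded normal, 2.0 v 1.3 | 1.02/0.97 | 86.2% | 85.3% | 84.7% | 9% |
| Rounded normal, 3.0 v 2.3 | 1.04/1.03 | 86.4% | 85.6% | 84.4% | 8% |
| Poisson, 1.4 v 0.7 | 1.19/0.84 | 89.5% | 86.2% | 86.0% | 38% |
| Poisson, 1.7 v 1.0 | 1.30/1.00 | 79.3% | 74.9% | 74.8% | 41% |
| Poisson, 2.0 v 1.3 | 1.41/1.14 | 71.9% | 66.8% | 66.7% | 12% |
| NB a=0.3, 1.4 v 0.7 | 1.42/0.92 | 81.0% | 74.3% | 74.7% | 25% |
| NB a=0.5, 2.0 v 1.3 | 2.00/1.46 | 48.8% | 39.1% | 41.1% | 42% |
| NB a=1.0, 2.0 v 1.3 | 2.43/1.73 | 37.2% | 26.7% | 28.1% | 53% |

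Normality was rejected in about 100% of trials in every row, including counts rounded from a normal distribution. A Lilliefors-type test gave the same answer. The power of the two-step rule is therefore the rank-sum power.

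**3. Cost of the switch (Student t minus rank-sum).** In the first three rows, where the SD is near 1, it is 1.5, 2.0 and 3.5 points. In the others it is 4.5, 5.2, 6.3, 7.7 and 9.1 points. A negative binomial likelihood-ratio test in a separate run (2,000 trials) had 87.8% against 85.8% for rank-sum (Poisson 1.4 v 0.7), 81.0% against 74.4% (a=0.3), and 44.8% against 38.7% (a=0.5).

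**4. Type I error.** With no treatment effect the two-step rule rejected in 5.3% (NB a=0.5, mean 2) and 5.5% (Poisson, mean 1.4) of trials.

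**5. SGRQ.** On continuous normal data with a difference of 0.7 SD (SGRQ plans 6/8.5 = 0.71), normality was rejected in about 10% of trials. The two-step power was 89.7% against 89.9% for the t test alone.

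**The case against.** - **The mean is among the listed summaries.** This stands. A reader might infer that the trial never tests or estimates the mean difference it was sized on. The document does not support that: a mean may be reported, and SGRQ would usually receive the t test if roughly normal. The fault is that the measure is not fixed.
- **No normality test is named.** This stands too. That counts always go to the rank-sum test holds only if a formal test is used; a judgement by eye could keep the t test.
- **Little power is lost.** Largely correct. The fall to between 28% and 41% in the last two rows comes mostly from SDs above the planned 1, and it hits the t test as well (37% and 49%). Against Welch's t test the rank-sum test loses practically nothing in the Poisson and NB rows. A much larger gap (about 12% to 18% for rank-sum against 40% to 44% for a rate-ratio test) appears only if all benefit falls on the 20% to 25% of patients with frequent exacerbations. That is an assumed worst case; the plan contains no such assumption.
- **Detail may sit in an unseen analysis plan.** An article may leave model details to that plan. Here, though, it states a rule for the primary outcomes, and that rule leads away from the measure used for sizing. The Bias control section mentions multivariate analysis and propensity scoring but does not tie them to the primary comparison.

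**Conclusion.** The point holds in a limited form. The stated rule makes the primary test depend on the data and leaves the effect measure open, while both endpoints were sized on mean differences. For exacerbations, any formal normality test at about 64:32 leads practically every time to a test that does not address 0.7 per year. If medians are then shown, they can be equal in both arms despite a true difference of 0.7, in about 8% to 53% of trials under the assumed rates and dispersion.

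The power cost is about 1 to 4 points near the planned SD and up to about 9 to 10 with overdispersion, against a Student t or rate-ratio test. A reader might infer a false-positive problem from the two-step choice; the simulations show none. SGRQ is affected less. The main harm is to interpretation, and it is worth correcting because the correction is cheap.

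**What to change.** Before unblinding, replace the normality-dependent choice with one named analysis per endpoint:
- **Exacerbations:** negative binomial model with log follow-up time as offset, giving a rate ratio with 95% CI. Report the mean rate in each arm so the result can be read against 0.7 per year.
- **SGRQ:** difference in mean change with 95% CI, read against 6 points, whatever the shape of the distribution.
- **Rank-sum test:** keep it as a labelled sensitivity analysis for both.

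If a separate analysis plan already names such analyses, it should say that they replace the published rule. The cost is a few sentences and no further patients or data. One small downside is that mean-based results give more weight to patients with very many exacerbations; the rank-sum sensitivity analysis shows how far that matters.

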### Outcome measures

All outcome measures will be recorded at baseline and during the intervention period (Table 2).

**Table 2 Tab2:** Study main measures and outcomes to be collected

Variable	Baseline (0-week)	1-month follow-up (4-weeks)	3-month follow-up (12-weeks)	6-month follow-up (26-weeks)	9-month follow-up (38-weeks)	12-month follow-up (52-weeks)
Primary Endpoint 1						
SGRQ scores	X	X	X	X	X	X
Primary Endpoint 2						
Number of exacerbations during the follow-up		X	X	X	X	X
Secondary Endpoints						
16S rRNA sequencing of sputum	X			X		X
Inflammatory factors	X			X		X
Oxidative stressors	X			X		X
Other Variables						
Clinical signs and symptoms	X	X	X	X	X	X
Transcutaneous regional oxygen saturation	X	X	X	X	X	X
BSI scores	X	X	X	X	X	X
mMRC dyspnea scores	X	X	X	X	X	X
HRCT grade, n (%)	X					X
Number of lesion lobes, n (%)	X					X
FEV1/FVC%	X			X		X
FEV1%	X			X		X
Number of exacerbations 12-months before the enrollment and during the trail	X	X	X	X	X	X
Time to first exacerbation		X	X	X	X	X
Time to second exacerbation		X	X	X	X	X
The longest duration of exacerbation in the last year	X					
The longest duration of exacerbation during the follow-up		X	X	X	X	X
Number of oral antibiotic therapies 12-months before the enrolment and during the trail	X	X	X	X	X	X
Number of intravenous antibiotic therapies 12-months before the enrolment and during the trail	X	X	X	X	X	X
Number of systemic glucocorticoid utilization12-months before the enrolment and during the trail	X	X	X	X	X	X
Number of hospitalization 12-months before the enrolment and during the trail	X	X	X	X	X	X

X means items should be evaluated or detected at the current follow-up

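### No baseline-adjusted model is named for the secondary markers, although each is already measured at week 0; adjusting for that value would gain power at almost no cost

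*Protocol article*

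**What the plan says.** Under Secondary endpoints, the protocol article names sputum 16S rRNA as the main secondary endpoint. It adds four inflammatory and four oxidative-stress markers, measured by ELISA in sputum and serum. Under Outcome measures it says "All outcome measures will be recorded at baseline and during the intervention period", and Table 2 marks 16S rRNA, the inflammatory factors and the oxidative stressors at weeks 0, 26 and 52.

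The Statistical analysis section singles out "The comparison between the NAC group and the control group in terms of 16S rRNA and the levels of inflammatory factors and oxidative stressors" as vital. That sentence gives no test, time point, scale or handling of baseline.

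The tests named around it are:
- a t test or Wilcoxon rank-sum test, chosen after a look at normality, for the primary outcomes;
- for the rest, the trial "will also use the t-test, chi-square test and Wilcoxon rank-sum test to evaluate baseline discrepancy and other variables".

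Regression appears in that section only for predictors of progression and indicators of NAC efficacy. The Bias control section says that final outcomes will be analysed with methods including multivariate analysis and propensity scoring, to control confounding. It names no covariates.

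**The concern.** The Study objective section lists the activity of NAC against bacteria, inflammation and oxidative stress as a key objective. The Sample size section sizes the trial for SGRQ and exacerbations only, so power for the markers is whatever 64 and 32 evaluable patients happen to give.

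If the markers were compared with the kind of test the section names, each patient's week-0 value would be collected and assayed but left out of the arm comparison. Two things would follow. Between-patient variation that baseline could explain would stay in the error term. With about 32 evaluable controls, a chance baseline difference between arms would also pass unadjusted into the week-52 estimate. Both cost precision, and both can be avoided with data the trial already schedules.

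**Working it through.** **Inputs from the article (Sample size).** Two-sided 5% level and 90% power; 64 NAC and 32 control evaluable, from "we design a ratio of 2:1 for the sample size of intervention group to control group"; for SGRQ a "mean difference (MD) of 6 points of SGRQ score as the smallest clinically important difference between two group with a standard deviation (SD) of 8.5"; for exacerbations an "MD of 0.7 times of exacerbation per year as the smallest clinically important difference between two group with a SD of 1 used in calculation"; and, on recruitment, "assuming 20% of patients in each group may drop out or lose data integrity, we need to recruit 79 in the intervention group and 40" (the last figure is for placebo).

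**Assumed inputs.** The article gives no effect size, SD or baseline-to-week-52 correlation (ρ) for any marker. I take a standardised effect of 0.5 (also 0.4), ρ of 0.3, 0.5 and 0.7, and both week-0 and week-52 values available for all 96 evaluable patients.

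**1. The plan's own figure.** Control-arm n = (1.960 + 1.282)² × SD² × (1 + 1/2) / MD².
- SGRQ: 10.51 × 72.25 × 1.5 / 36 = 31.6, so 32 controls and 64 NAC, as stated. Power at 64:32 is 90.3% (89.7% by noncentral t).
- Exacerbations: 10.51 × 1.5 / 0.49 = 32.2, so 33 and 66. Power at 64:32 is 89.9% (89.3% by noncentral t), in effect the stated 90%.
- Dropout: 32/0.8 = 40 and 64/0.8 = 80, against the stated 40 and 79. The difference is immaterial here.

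So 64:32 is a fair basis for the marker comparison.

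**2. Power for a marker at week 52.** With d the standardised effect, power ≈ Φ(d × √(64 × 32 / 96) / f − 1.96), and √(64 × 32 / 96) = 4.62. The factor f is the residual SD relative to the week-52 SD:
- week-52 value alone: f = 1
- change from baseline: f = √(2(1 − ρ))
- ANCOVA on the week-0 value: f = √(1 − ρ²)

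For d = 0.5 with no adjustment: 0.5 × 4.62 − 1.96 = 0.35, and Φ(0.35) = 64%. For ANCOVA at ρ = 0.5: 2.31 / 0.866 − 1.96 = 0.71, and Φ(0.71) = 76%.

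| ρ | Week 52 alone, d = 0.5 | Change, d = 0.5 | ANCOVA, d = 0.5 | Week 52 alone, d = 0.4 | ANCOVA, d = 0.4 | 96 patients act like, 96/(1 − ρ²) |
|---|---|---|---|---|---|---|
| 0.3 | 64% | 50% | 68% | 46% | 49% | 105 |
| 0.5 | 64% | 64% | 76% | 46% | 57% | 128 |
| 0.7 | 64% | 85% | 90% | 46% | 74% | 188 |

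The effect detectable with 80% power, (1.960 + 0.842) × f / 4.62, falls from 0.61 SD unadjusted to 0.58, 0.53 and 0.43 SD with ANCOVA. Change scores are worse than ignoring baseline when ρ is below 0.5.

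**3. What the log scale contributes.** Simulated log-normal markers, 64:32, effect 0.5 log-SD, 2,000 trials per setting, log-SD from 0.5 to 1.5:
- raw-scale t test: about 60%, falling to 40% as skewness grows
- rank-sum: 59% to 62%
- log-scale t test: 62% to 64%
- log-scale ANCOVA: 66% to 68%, 73% to 74% and 87% to 90% at ρ = 0.3, 0.5 and 0.7
- raw-scale ANCOVA at log-SD 1.0: 52%, 57% and 68% at the same ρ

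Against a rank-sum test, logging alone adds 2 to 3 points. It matters more inside the ANCOVA: on strongly skewed raw values, much of the benefit of adjustment is lost.

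**4. A second scenario.** With a true NAC/control ratio of 0.65 and log-SD 1.0, simulation gives rank-sum 48% against log-scale ANCOVA 55%, 62% and 77% at ρ = 0.3, 0.5 and 0.7. Type I error is about 5%.

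**The case against.** A reader might infer that the trial has decided to compare the markers without their week-0 values. The article does not say so. The marker sentence assigns no test. The list in "will also use the t-test, chi-square test and Wilcoxon rank-sum test to evaluate baseline discrepancy and other variables" refers to a category that Table 2 sets apart from the secondary endpoints, and the t-or-Wilcoxon choice is stated for the primary outcomes. Nothing excludes adjustment or transformation. The article is a condensed account, and a statistical analysis plan, where covariates and scales are commonly set, may exist but is not shown. This objection stands. The point can only be that no baseline-adjusted model is named and that every between-arm test named is unadjusted.

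The Bias control section is a second defence, since it mentions multivariate analysis. It shows that the authors do not confine themselves to two-group tests. It does not supply the adjustment, however: it is directed at confounding and names no baseline marker values. Here the purpose is precision in a randomised comparison.

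A reader might also infer that the named tests would give wrong answers. They would not. Type I error stays near 5%, and chance imbalance under randomisation costs precision without biasing the test.

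Third, it is tempting to give the log scale equal weight. Because a rank-sum test on week-52 values is unchanged by a log, that half is small. Nor does logging settle 16S rRNA, the main secondary endpoint: the article does not say which 16S summary is compared.

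**Conclusion.** The point holds as an optional efficiency improvement, not as an error or a contradiction. The article names no model that uses the week-0 marker values it schedules, and the tests it does name, though valid, would leave power unused if applied to the markers. At 64:32 and a standardised effect of 0.5, the gain from adjustment is about 4, 12 and 26 percentage points at ρ = 0.3, 0.5 and 0.7 (64% to 68%, 76% and 90%). These sizes rest on the assumed effect, the assumed correlations and complete pairs of samples. At ρ = 0.3 the gain is small. The direction does not depend on the exact inputs so long as baseline and week-52 values are correlated and the model is fitted on a suitable scale.

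**What to change.** In the Statistical analysis section, or in the analysis plan if one exists, state that:
- each sputum and serum ELISA marker is compared at week 52 by ANCOVA, with arm and the week-0 value of the same marker in the model;
- markers that are right-skewed are analysed on the log scale (outcome and covariate) and reported as the NAC/control geometric mean ratio with a 95% confidence interval;
- the rank-sum test serves as a sensitivity check;
- any 16S summary measure is likewise adjusted for its own week-0 value, on a scale that suits that measure.

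The cost is wording only: the week-0 and week-52 samples are already in Table 2, and no patients or visits are added. The one small downside is that values below the assay limit need a fixed rule before they are logged. The Randomisation and double-blind section defers unblinding and analysis until all participants have finished follow-up, so the text can properly be settled before then.

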**Methods:**

NINCFB is a prospective, multicentre, double-blind, randomised, placebo-controlled trial that will recruit 119 patients with NCFB and randomly divide them into an NAC group (*n* = 79) and a control group (*n* = 40). Participants in the NAC group will receive 600 mg oral NAC twice daily for 52 weeks, while patients in the control group will receive 600 mg placebo twice daily for 52 weeks. The information at baseline will be collected once participants are enrolled. The primary endpoints are the changes in St George’s Respiratory Questionnaire scores and the number of exacerbations in 52 weeks. The secondary endpoints are the 16S rRNA of sputum and the levels of inflammatory factors and oxidative stressors in sputum and serum. Other data related to radiography, lung function tests, number of oral and/or intravenous antibiotic therapies and adverse events (AEs) will also be analysed. Further subgroup analysis distinguished by the severity of disease, severity of lung function, airway bacterial colonization and exacerbation frequency will be performed.

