### Bias control

The inclusion and exclusion criteria of this study are clearly designed to reduce selection bias. Detailed data collection and strict quality management procedures will be formulated. All procedures are in accordance with the unified standard operating procedure (SOP), and trial-related tests will be conducted by experts at West China Hospital of Sichuan University to ensure the consistency of the results and reduce information bias. The final outcomes will be analysed by comprehensive statistical methods such as standardization, multivariate analysis, and propensity scoring to control for confounding factors.

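### Time to first and second exacerbation fall under tests that take no account of censoring, and no survival method is named

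*Protocol article*

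**What the plan says.** Table 2 (Outcome measures) has a block headed "Other Variables". It includes "Time to first exacerbation" and "Time to second exacerbation", both recorded at every follow-up visit from week 4 to week 52.

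The Statistical analysis section covers variables outside the primary and secondary endpoints in one sentence: "NINCFB will also use the t-test, chi-square test and Wilcoxon rank-sum test to evaluate baseline discrepancy and other variables". Two other statements on method could be relevant. The same section says "Regression analysis and the correlation coefficient may confirm the predictors of disease progression and indicators of NAC efficacy", which concerns prediction and is only a possibility. Bias control refers to "comprehensive statistical methods such as standardization, multivariate analysis, and propensity scoring to control for confounding factors". Kaplan-Meier, log-rank and Cox are not mentioned anywhere.

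Three further statements matter. Follow-up ends at 52 weeks. Sample size allows for 20% dropout or loss of data integrity in each group. Adverse events has patients leave the study once an event is judged drug-related. Data collection codes missed visits as incomplete, and no rule gives a time value to a patient who has no event or who leaves early.

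**The concern.** Both variables are right-censored. A patient with no exacerbation by week 52, or who leaves before having one, has no observed time. A t-test or rank-sum test needs a number for every patient analysed, so someone must decide what such patients contribute. The article names the tests and leaves that decision open.

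Censoring would be substantial. The Background reports that half of patients with this disease have two or more exacerbations a year, so about half would have no second event in a year. The trial recruits patients with recent exacerbations, so its own share may be lower. Exit after drug-related adverse events could also differ between arms.

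At stake is whether a real delay is shown at its true size and, if exit is unequal, whether an apparent difference in time is an artefact of shorter observation in one arm.

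**Working it through.** **Inputs from the article.** 79 NAC and 40 placebo patients (2:1), 52 weeks, two-sided 5% level, a difference of 0.7 exacerbations per year, 20% dropout. The article gives no figure for either time variable, so there is none to reproduce.

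**Assumptions.** The article gives no control rate, so 1.2 to 2.5 per year is used, with the NAC rate 0.7 lower. Event rates are constant, and dropout is random at a constant rate.

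**Step 1: share with no event, complete follow-up.** With rate r per year, P(no first event) = e^-r and P(fewer than two) = e^-r(1 + r). At 2.0 versus 1.3:
- no first event: 14% placebo, 27% NAC
- no second event: 41% placebo, 63% NAC

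**Step 2: first-event delay if event-free patients are excluded.** The mean among patients with an event is 52 × [1/r − e^-r/(1 − e^-r)]. The like-for-like target is the 52-week restricted mean, 52 × (1 − e^-r)/r. At 2.0 versus 1.3:
- events only: 17.9 and 20.5 weeks, a difference of 2.7 (from unrounded means)
- restricted mean: 22.5 and 29.1 weeks, a difference of 6.6
- hidden: 1 − 2.7/6.6, about 60%

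| Rates per year, placebo vs NAC | Events-only delay (weeks) | Restricted-mean delay (weeks) | Hidden |
|---|---|---|---|
| 1.2 vs 0.5 | 2.9 | 10.6 | 73% |
| 1.5 vs 0.8 | 2.8 | 8.9 | 68% |
| 2.0 vs 1.3 | 2.7 | 6.6 | 60% |
| 2.5 vs 1.8 | 2.4 | 5.0 | 51% |

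**Step 3: simulated power with 20% dropout (1,500 runs per row).** *Events only* excludes patients without an event (the larger of t-test and rank-sum is shown). *Last seen* enters the exit date or week 52 as if it were the event time.

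| Placebo rate | Event | Log-rank | Events only | Rank-sum, last seen |
|---|---|---|---|---|
| 1.2 | first | 0.92 | 0.11 | 0.80 |
| 1.5 | first | 0.73 | 0.13 | 0.58 |
| 2.0 | first | 0.50 | 0.12 | 0.37 |
| 2.5 | first | 0.35 | 0.13 | 0.26 |
| 1.2 | second | 0.89 | 0.06 | 0.55 |
| 1.5 | second | 0.79 | 0.08 | 0.55 |
| 2.0 | second | 0.62 | 0.09 | 0.43 |
| 2.5 | second | 0.49 | 0.10 | 0.34 |

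Under last-seen handling the loss against log-rank is 9 to 15 points for the first event and 15 to 34 for the second. The observed first-event delay is 4.5 to 9.5 weeks, against restricted means of 5.0 to 10.6, so nearly 90% stays visible.

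**Step 4: no true effect, unequal exit.** With 1.5 events per year in both arms and early exit of 30% (NAC) and 10% (placebo), 3,000 runs give a type I error under last-seen handling of 0.09 to 0.10 for the first event and 0.25 for the second. Log-rank stays at about 0.05. The exit rates are an illustration, not a forecast.

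**The case against.** The strongest reply is that the link between variables and tests is inferred. The sentence in Statistical analysis names neither time variable, and the narrative section on other variables does not mention them. The connection is the shared label in Table 2. This is also a condensed article, and a censoring rule may sit in a fuller plan. Part of this stands: the article does not expressly prescribe a t-test for time to exacerbation. But it does name tests for a class of variables that contains these two, and the named tests do not fit them. That differs from silence.

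A reader might infer three stronger claims that the article does not support.

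- *The tests cannot deal with event-free patients at all.* They can if follow-up is complete. A rank-sum test that ranks event-free completers last then has first-event power of 0.28 to 0.90, against 0.36 to 0.92 for log-rank. Even with 20% dropout, setting event-free completers to 52 weeks and dropping early exits without an event costs only 1 to 13 points across both variables.
- *Most of a real delay would be hidden.* This holds only if event-free patients are excluded, which the article nowhere says. Setting the median difference at 2.0 versus 1.3 per year (27.7 − 18.0 = 9.7 weeks) against the 2.7-week events-only difference would also mix two different quantities. The fair comparator is 6.6 weeks.
- *The bias always runs towards no difference.* Unequal early exit can create a difference where none exists, as Step 4 shows. Nor are the excluded patients simply those in whom the drug worked: at 2.0 per year, 14% of placebo patients would also be event-free.

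**Conclusion.** The point holds in a conditional form. As written, the article places two censored variables under tests that ignore censoring and names no method that would handle them. Excluding event-free patients hides 51% to 73% of the 52-week first-event delay and leaves power at about 0.10 to 0.13 (first event) and 0.06 to 0.10 (second). Last-seen handling keeps most of the delay visible but loses power and is vulnerable to unequal exit.

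These sizes rest on assumed control rates, constant event rates and random exit. The log-rank type I error near 0.05 likewise assumes that exit is unrelated to exacerbation risk. The variables are neither primary nor secondary endpoints and do not drive the sample size. The main test of exacerbations is the count, "the number of exacerbations in 52 weeks". Priority is low to moderate.

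**What to change.** Add one sentence to Statistical analysis: time to first and time to second exacerbation, both measured from randomisation, will be analysed by Kaplan-Meier curves, a log-rank test and a Cox model (hazard ratio with 95% confidence interval), with patients censored at week 52 or at last contact if earlier. State that these two variables are excepted from the sentence on the t-test, chi-square and rank-sum tests.

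The cost is that sentence. The sample size does not change, and the analysis uses event times already listed in Table 2 plus the date of last contact. Randomisation and double-blind has unblinding and analysis start only after all follow-up is complete, so the change can be fixed while the data are still blinded.
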